### Examination procedure and randomisation

After recruitment, the eligible participants will take part in the baseline evaluation. They will complete a questionnaire on sociodemographic, symptomatology and comorbidity, and three self-reported questionnaires on pain and disability: the Neck Disability Index (NDI), the short version of the Disabilities of the Arm, Shoulder and Hand Questionnaire (*Quick*DASH), and a numerical pain rating scale (NPRS). Finally, they will undergo a physical examination of the cervicothoracic spine, which will include the evaluation of cervicothoracic range of motion using a CROM (cervical inclinometers).

After baseline evaluations, assignation of patients to either the conventional or experimental intervention will be performed. To reduce contamination bias, the two programs will be given in different clinics. An independent research assistant will open the randomisation envelope indicating the participant's assignment to the group of clinics that corresponds to the experimental or control group. The research assistant will be blind to the baseline evaluation results and to the assignation of which clinic is providing which intervention. The research assistant will give the list of the clinics providing the rehabilitation program assigned to the participant, and the participant will choose the clinic of their choice. Random number generator will be used to establish randomisation lists prior to the initiation of the study. A member of the research team not involved with data collection will generate the randomisation list. To make sure that two equal groups of 18 subjects will be obtained, blocked randomisation will be used (block size of 6). Three physical therapy clinics will provide the control rehabilitation program and three different clinics the experimental rehabilitation program.

At the end of the 4-week rehabilitation program (maximum 3 days after the last treatment session), and four weeks after the end of the program, the three self-reported questionnaires (NDI, *Quick*DASH, and NPRS), as well as cervicothoracic range of motion will be revaluated. Furthermore, at the two follow-up evaluation sessions, a question pertaining to global change since the initial session (*Global rating of Change *[GRC]) will be completed. An independent physiotherapist, blind to the group assignment, will perform the evaluations according to standardised procedures.

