*Conventional Rehabilitation Program: *The conventional program will consist in cervicothoracic mobilisations and stabilization exercises. This program is based on the intervention used in clinical practice [46] and on programs proposed in two RCTs evaluating individuals with neck and arm pain that do not include any specific mobilisation or exercise leading to the opening of the intervertebral foramen [22,47]. In the present study, four mobilisation techniques (10 repetitions * 30 seconds for each technique) will be executed at each treatment session. The mobilisation techniques will be chosen by the physiotherapist according to the results of the biomechanical examination performed at the beginning of each session. The physiotherapists will be allowed to use any of the following manual therapy techniques: rotations, lateral glides, postero-anterior glides, infero-medial glides or supero-anterior glides mobilisations. The physiotherapists will choose the techniques based on the patient's response to the mechanical assessment. However, the physiotherapists will not be allowed to use techniques that specifically open the intervertebral foramen of the affected segment, two segments above and two segments below. Following the mobilisation techniques, a 5-minute global manual traction (5 * 1 minute) will be applied. Although global manual traction causes an increase in diameter of the intervertebral foramen, it is not specific to the affected segment. The force for manual tractions will be the applied force causing a 50% decrease in cervical pain. Finally, a standardised home exercise program will be taught to the patients. The program, in line with best practice [48], will contain strengthening exercises for the neck flexors (longus colli, longus capitis, and rectus capitis anterior; 10 repetitions * 10 seconds, once/day in dorsal decubitus), axial extension exercises (10 repetitions * 5 seconds, once/day sitting) and one exercise chosen by the physiotherapist based on the deficits observed during the biomechanical exam. The third exercise will be chosen among: cervical or thoracic active range of motion mobility, cervical extension strengthening, or scapular strengthening. However, no exercise leading to the specific opening of the intervertebral foramen ipsilateral to the lesion will be given. Standardised postural advices will also be given.

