### Sample size and Analyses

The sample size calculation is based on the primary outcome measure, the NDI. The NDI has a clinically important difference of 7/50 (14/100) points for patients presenting a cervical radiculopathy. The standard deviation reported in the literature for this population is 18.4 [33]. The considered parameters are 0,05 for type I error (α) with a power of 0,80 (1-β). For an analysis of variance (ANOVA), the sample size required is 16 subjects per group. However, 18 subjects per group will be recruited to compensate for withdrawals and probable loss of follow-up. This sample size will provide sufficient power to detect a clinically important difference between the two groups.

Descriptive statistics (mean, standard deviation, median frequency counts) will be calculated for all outcome measures at the different times of measurement (week 0, 4 and 8) to summarise results. Baseline demographic data will be compared (independent Student t-tests and Chi-squared tests) across groups to establish the comparability of covariables. If needed, statistical adjustments will be made for baseline characteristics that are significantly different between groups. All data will be tested to ensure they meet the assumptions for the inferential statistical analyses. If they do not meet the necessary assumptions, appropriate non-parametric procedures will be used. An intention-to-treat analysis will be used in which all participants will be analysed in the group to which they were originally assigned. All dropouts and the reason for dropping out of the study will be reported. Any harms or unintended effects during the rehabilitation programs will be recorded, reported and discussed.

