A mixed-model, 2-way ANOVA (Groups [experimental program, conventional intervention] × Evaluation [week 0, 4 and 8]) will be used to analyse the effects of the rehabilitation programs. Separate analyses will be conducted on each of the primary (NDI) and secondary (*Quick*DASH, NPRS, cervicothoracic range of motion) outcomes. If an interaction is detected (*P *< 0.05), simple effects will be examined. The Kolmogorov-Smirnov test (*P *< 0.05) will be conducted on the different scores to ensure normality for all variables with significant main effects. For normally distributed variables with significant main effects, post hoc dependent Student *t *tests will be conducted and effect sizes (Cohen's *d*) will be calculated. Effect sizes will be interpreted as small (0.20), medium (0.50), or large (0.80). For any variables that will not be normally distributed, the Wilcoxon signed-rank test and Glass's delta (effect size) will be used for post hoc contrasts. Since this study is looking at a new rehabilitation program, patient's perceived change following the programs will also be categorised as either success or failure. Success will be defined as a 50% improvement in NDI score and a GRC score rated as "moderately better" (+3) or higher. Patients will be classified as failure if the change on the GRC is "somewhat better" (+2) or at any level below this or if there is not a 50% improvement in the NDI [49]. The proportion of success/failure will be compared across groups (Chi-squared tests).

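### Each program runs in its own three clinics, but the primary ANOVA and the sample size ignore clinic: if outcomes differ between clinics, that difference is inseparable from the program effect and the 5% test is too liberal

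*Protocol article*

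**What the plan says.** Under Examination procedure and randomisation, patients are randomised individually in blocks of six, 18 per arm, to a group of clinics: "Three physical therapy clinics will provide the control rehabilitation program and three different clinics the experimental rehabilitation program". The reason is given: "To reduce contamination bias, the two programs will be given in different clinics". The patient receives the list for the assigned arm, and "the participant will choose the clinic of their choice". How the six clinics were divided between the programs is not described.

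Under Rehabilitation Programs, the conventional arm leaves the four mobilisation techniques to the therapist, within a permitted list: "The mobilisation techniques will be chosen by the physiotherapist according to the results of the biomechanical examination" at each session. In the experimental arm two of the four are mandatory and two are chosen.

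Under Sample size and Analyses, the model is "A mixed-model, 2-way ANOVA (Groups [experimental program, conventional intervention] × Evaluation [week 0, 4 and 8", applied separately to each outcome. The sample size uses a difference, a standard deviation, alpha and power. Neither the model nor the calculation mentions clinic, therapist, an ICC or a design effect.

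**The concern.** Randomising patients balances patients between arms, but not the people who treat them. Every clinic, and so every treating physiotherapist, belongs to one arm only. Two consequences follow if clinics differ in the results they obtain.

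- **Aliasing.** The difference between the two sets of clinics is part of the estimated program effect. Clinic cannot be fitted as a fixed effect beside group, because clinic determines group.
- **Precision.** Patients treated in the same clinic have correlated outcomes. A model that treats them as independent understates the standard error and rejects a true null hypothesis too often.

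The treatment is hands-on and partly at the therapist's discretion, so some clinic variance is plausible. At stake is the interpretation: the trial wants to credit benefit to opening the foramen and hopes to inform practice guidelines, while a positive result could partly reflect which clinics delivered which program.

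**Working it through.** **The plan's own figure.** The stated inputs are a difference of 14/100, SD 18.4 (read here as the 0-100 scale), alpha 0.05 and power 0.80. Without clustering, n = 2(1.96 + 0.84)² × (18.4/14)² = 27.1, so 28 per group two-sided (29 with the t distribution). The stated 16 is reached only with an unstated within-patient correlation. That is a separate matter, and nothing below depends on it. What matters here is that the calculation contains no clinic term.

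**Inputs.** Three clinics and 18 patients per arm come from the article. An even spread gives m = 18/3 = 6 patients per clinic; this is an assumption, because patients choose. The ICC is assumed over a range.

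**Standard error.** The design effect is DE = 1 + (m − 1) × ICC, and the true standard error is √DE times the patient-level one. A normal approximation to the real type I error is 2 × [1 − Φ(1.96/√DE)]. The simulated column shows the range over separate runs of at least 40,000 trials each, using a patient-level t-test at one time point.

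| Assumed ICC | DE | √DE | 1.96/√DE | Type I, approximate | Type I, simulated |
|---|---|---|---|---|---|
| 0.01 | 1.05 | 1.025 | 1.913 | 5.6% | 5.6-5.7% |
| 0.02 | 1.10 | 1.049 | 1.869 | 6.2% | 6.1-6.2% |
| 0.05 | 1.25 | 1.118 | 1.753 | 8.0% | 7.6-8.0% |
| 0.10 | 1.50 | 1.225 | 1.600 | 11.0% | 10.6-11.4% |

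A smaller simulation of the group-by-evaluation interaction itself (4,000 runs) gave about 6%, 8-9% and 10-15% at ICC 0.02, 0.05 and 0.10, depending on the assumed within-patient correlation.

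**Uneven clinics.** Replace m by Σn²/Σn. For 10/5/3 patients, m = 134/18 = 7.44, and simulated type I error is 6.4-6.6%, 8.7-8.9% and 12.6-13.0% at ICC 0.02, 0.05 and 0.10. For 12/4/2, m = 164/18 = 9.11, and it is about 10% at 0.05 and 15% at 0.10.

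**Aliasing.** With three clinics per arm, clinic effects alone give the arm difference a standard deviation of √(2 × ICC × 18.4²/3).

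- ICC 0.05: √(2 × 0.05 × 338.56/3) = 3.4 points.
- ICC 0.10: √(2 × 0.10 × 338.56/3) = 4.8 points.

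The target difference is 14 points on the same scale.

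**Price of a valid clinic-level test.** The standard error of the difference in clinic means is 18.4 × √{(2/3) × [ICC + (1 − ICC)/6]}. At ICC 0.05 this is 18.4 × √(0.6667 × 0.2083) = 6.86, so the noncentrality is 14/6.86 = 2.04. On 4 degrees of freedom the power is about 0.35. The patient-level t-test with 18 per arm has power of about 0.60 when the ICC is zero.

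**The case against.** The strongest reply is that the inflation is conditional. A reader might infer that the error bars are certainly too narrow. The article does not support that: it gives no ICC, and at 0.01-0.02 the effect is minor. That part of the reply stands.

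Several features also limit clinic variance. The arms share the number and length of sessions and the number of techniques and exercises. The opening examination and the recording forms are standardised. Part of the experimental treatment is mandatory. All outcomes are measured at one outside site by a blinded evaluator who treats no one, so clinics cannot differ in how they measure. This weakens the case for the upper end of the range, but differences in delivery remain. Nor does the baseline score cancel them, because baseline is measured before a clinic is assigned.

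Separate clinics are a deliberate choice. They guard against contamination, which would shrink the difference between programs, and they support patient blinding. That justifies the design, but the analysis must then reflect it.

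A reader might also infer that better clinics were steered to one arm. The article is silent on how clinics were assigned, which a condensed report may be, and silence is not evidence of a biased assignment.

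Finally, one could leave clinic to a statistical analysis plan. For a sensitivity analysis that is fair. It is weaker for the primary model and the sample size, because the article fixes the factors of one and the inputs of the other.

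**Conclusion.** The concern holds in conditional form: the stated analysis does not match the stated delivery. If the clinic ICC is above zero, clinic and program effects cannot be separated and the nominal 5% test is anti-conservative. The effect is small at an ICC of 0.01-0.02 and material from about 0.05. These figures rest on an assumed ICC, about six patients per clinic and a single-time-point test standing in for the group contrast.

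Two stronger conclusions are not supported. The documents do not show that a positive result would be false. Nor do they show that a clinic-level test must replace the primary analysis: with six clinics it has 4 degrees of freedom and low power, so its use as the primary analysis is debatable. This is a point that should be fixed, not one that invalidates the trial.

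**What to change.** 1. Record the clinic and therapist for every patient. Add a sensitivity analysis that accounts for clinic, either a random clinic effect with small-sample degrees of freedom (Kenward-Roger or Satterthwaite) or a comparison of clinic means on 4 degrees of freedom. Report the estimated clinic variance.
2. State in the sample-size section that the power assumes no clinic variance.
3. Limit the conclusion to the two programs as delivered in these clinics, and do not extend it to foraminal opening as such.
4. If the clinics are not yet assigned, assign the six to the two programs at random. Otherwise report how they were assigned.

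The cost is two recorded items per patient, a few sentences and, where still possible, one random draw. The downside is that the clinic-level analysis will give wide intervals, its variance estimate will be poor, and its power is about 0.35 for 14/100 at ICC 0.05. Random assignment of clinics guards against systematic imbalance, but a chance difference between two sets of three clinics remains aliased with program. Only delivery of both programs within clinics, or more clinics, would reduce that, and the first would reopen the contamination problem that the design avoids.

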### Blinding

A double-blind design will be used, in which the participants and evaluators will be blinded. Due to the nature of the intervention, it is not possible to blind the treatment provider to the treatment given. However, we think that the participants can be blinded since they will not be aware of the precise type of mobilisations received and to reduce potential contamination bias, the two programs will be given in different clinics. To evaluate the effectiveness of the blinding, the participants and the evaluator will complete a questionnaire related to their opinion of the allocation at the week-4 follow-up evaluation. We will blind the evaluator performing the outcome evaluations and the evaluation session will take place outside the treating clinics. The evaluator and treatment providers will be different physiotherapists. Patients will be instructed not to discuss the specific mobilisation techniques and exercises received with the evaluator. At the end of study, participants will be informed of their group allocation.

### Outcome measures (dependent variables)

The NDI questionnaire has been chosen as the primary outcome measure. All evaluations will be undertaken at the CIRRIS. Here is a description of the outcome measures:

*Neck Disability Index: *The NDI is a 10-item questionnaire that measures a patient's self-reported neck pain related disability. Questions include activities of daily living, such as: personal care, lifting, reading, work, driving, sleeping, recreational activities, pain intensity, concentration and headache. The questions are measured on a six-point scale from 0 (no disability) to 5 (full disability). The numeric response for each item is summed for a total score ranging from 0 to 50 [32]. A higher NDI score indicates a greater patient's perceived disability. The reliability (intraclass correlation coefficient [ICC]: 0.73 to 0.98), construct validity, and responsiveness to change have all been demonstrated in various populations [32]. For patients with cervical radiculopathy, the minimal detectable change is 10 points, and the clinically important difference is 7 points [33]. The validated French version of the NDI will be used [34].

*Disabilities of the Arm, Shoulder and Hand: *The *Quick*DASH is a region-specific questionnaire that evaluates the physical disability and symptoms of the upper limb in patients with upper extremity disorders [35]. It consists of 11 items extracted from the original 30-item DASH. Each item has five response choices, ranging from "no difficulty or no symptoms" to "unable to perform activity or very severe symptoms," and is scored on a one-to-five scale. To calculate a *Quick*DASH score at least 10 of the 11 items must be completed. The score ranges from 0 (no disability) to 100 (most severe disability). The validity, reliability (ICC = 0.96) and responsiveness of the *Quick*DASH have been established [36]. The minimal detectable change is 10.8% and the clinically important difference is 10.2% [36]. The *Quick*DASH is also valid for the measurement of upper extremity disability in patients presenting neck pain [37]. The validated French-Canadian version of the *Quick*DASH will be used [38].

*Numerical Pain Rating Scale: *The level of upper limb and neck pain will be captured separately with the NPRS. Using an 11-point scale, ranging from 0 (no pain) to 10 (worst pain imaginable), participants will be asked to answer the following question: "*On a scale of 0 to 10, where 0 corresponds to no pain and 10 to the worst imaginable pain, evaluate the intensity of your neck pain at this moment*". The same question will be asked for the upper limb. The NPRS is frequently used in clinical studies in association with the NDI [22,39,40]. The NPRS is moderately reliable (ICC = 0.76) [39], and has a clinically important difference of 20% [40].

*Cervicothoracic Mobility: *The CROM measures cervical range of motion for rotation, flexion/extension, and lateral flexion using three separate inclinometers attached to a frame similar to eyeglasses: one inclinometer in the transverse plane for rotation, one inclinometer in the sagittal plane for flexion/extension, and one in the frontal plane for lateral flexion [41]. The rotation inclinometer has a magnetic needle, whereas the flexion/extension and the lateral flexion inclinometers have gravity needles. All subjects will be seated in a standardised position during the examination. Three measures will be conducted in each direction and the means will be used for data analysis. The reliability (ICC = 0.89-0.90) and construct validity of the CROM have been established [41].

*Global Rating of Change: *GRC questions are designed to quantify a patient's perceived improvement or deterioration over time. Using a 15-point GRC scale, ranging from -7 (a very great deal worse) to 0 (about the same) to +7 (a very great deal better), participants will be asked to answer the following question: "*Overall, has there been any change in your condition since the initial evaluation? Please indicate if there has been any change in your condition by choosing one of the following options*" [42]. The validity, reliability (ICC = 0.90) and responsiveness of GRC scales have been established [43].

### Rehabilitation Programs (independent variables)

Physiotherapists working in six physiotherapy clinics in the Quebec City area will provide the rehabilitation programs. Each participant will receive eight physiotherapy treatment sessions during a 4-week span (2 sessions/week; 30 to 45 minutes each session) and will perform a home exercise program. At the beginning of each session, the physiotherapist will conduct a standardised biomechanical examination of the cervicothoracic spine. It will consist of an intervertebral segmental mobility evaluation using lateral glides at the cervical spine and postero-anterior glides at the thoracic spine (T1 to T6). Segmental mobility will be rated as normal, hypomobile or hypermobile. Sandmark & Nisell and Rey-Eiriz et al. demonstrated that this rating of cervicothoracic mobility is sensitive (> 0.80) and specific (> 0.70) [44,45]. Furthermore, this evaluation of segmental mobility is recommended in the *Neck Pain Clinical Practice Guide *of the *American Physical Therapist Association *[5]. The results of the biomechanical examination, as well as the nature and intensity of the intervention, will be documented using standardised forms.

*Conventional Rehabilitation Program: *The conventional program will consist in cervicothoracic mobilisations and stabilization exercises. This program is based on the intervention used in clinical practice [46] and on programs proposed in two RCTs evaluating individuals with neck and arm pain that do not include any specific mobilisation or exercise leading to the opening of the intervertebral foramen [22,47]. In the present study, four mobilisation techniques (10 repetitions * 30 seconds for each technique) will be executed at each treatment session. The mobilisation techniques will be chosen by the physiotherapist according to the results of the biomechanical examination performed at the beginning of each session. The physiotherapists will be allowed to use any of the following manual therapy techniques: rotations, lateral glides, postero-anterior glides, infero-medial glides or supero-anterior glides mobilisations. The physiotherapists will choose the techniques based on the patient's response to the mechanical assessment. However, the physiotherapists will not be allowed to use techniques that specifically open the intervertebral foramen of the affected segment, two segments above and two segments below. Following the mobilisation techniques, a 5-minute global manual traction (5 * 1 minute) will be applied. Although global manual traction causes an increase in diameter of the intervertebral foramen, it is not specific to the affected segment. The force for manual tractions will be the applied force causing a 50% decrease in cervical pain. Finally, a standardised home exercise program will be taught to the patients. The program, in line with best practice [48], will contain strengthening exercises for the neck flexors (longus colli, longus capitis, and rectus capitis anterior; 10 repetitions * 10 seconds, once/day in dorsal decubitus), axial extension exercises (10 repetitions * 5 seconds, once/day sitting) and one exercise chosen by the physiotherapist based on the deficits observed during the biomechanical exam. The third exercise will be chosen among: cervical or thoracic active range of motion mobility, cervical extension strengthening, or scapular strengthening. However, no exercise leading to the specific opening of the intervertebral foramen ipsilateral to the lesion will be given. Standardised postural advices will also be given.

*Rehabilitation program targeting the opening of intervertebral foramen*: The same program as for the conventional rehabilitation program will be applied, with two exceptions:

• Of the four mobilisation techniques, there will be two mandatory techniques targeting the opening of the intervertebral foramen on the same side and at the same level as the radiculopathy: global contralateral rotation mobilisation and ipsilateral lateral glide in a flexion position (10 repetitions * 30 seconds for each technique). The physiotherapist, according to the biomechanical evaluation results, will choose the two other mobilisation techniques including rotations, lateral glides, postero-anterior glides, infero-medial glides or supero-anterior glides mobilisations.

• The third exercise of the home program will be an opening technique: contralateral rotation exercise (contralateral to the affected segment; 10 repetitions * 3 seconds, 10 times/day).

Therefore, the number of mobilisation techniques and home exercises will be the same for the two intervention groups.

